**Fig. 1 Fig1:**
[figure not shown]
Conceptual model of study design

## Methods

### Design

This study is an RCT comparing two conditions: FAST-blended (FASTb; *n* = 100) and FAST-regular (FASTr; *n* = 100). The study has a multi-method (self-report, case-file analysis, and judicial file coding) and multi-informant (juveniles, caregivers, and therapists) design with four waves: pre-test, post-test, 6-month follow-up, and two-year follow up. To examine mechanisms of change in the total group (*n* = 200), monthly assessments of key variables are added during the treatment period. The study was registered at ClinicalTrials.gov on 07/11/2022 (NCT05606978). See Fig. 2 for the study flowchart and Table 1 for an overview of the various constructs, informants, and timing of assessments.

**Fig. 2 Fig2:**
[figure not shown]
Flowchart of study design

### Setting

FAST is offered by de Waag, an outpatient forensic mental health care center with 12 treatment sites in the Netherlands. Clients are referred by the juvenile justice system or voluntarily by mental healthcare facilities, school care coordinators, or general practitioners. FAST therapist teams at six treatments sites, located in Almere, Amersfoort, Amsterdam, Den Haag, Leiden, and Utrecht approach participants for the study. Participants will be recruited between 14 and 2022 and June 2025.

**Table 1 Tab1:** Concepts, instrument, and informants at the different assessment points

Variable type	Instrument	Respondent					Assessment				
		Ju	Ca	Th	CF	JR	T1	M	T2	T3	T4
Primary outcome	YSR	x					x	x	x	x	
	CBCL		x				x	x	x	x	
	SDB	x					x	x	x	x	
	Out of home placement (case file)*				x		x		x		
	Out of home placement questionnaire	x	x						x	x	
	RAF GGZ Youth*				x		x		x		
	Convictions					x					x
Secondary outcome	Peilstation Middelengebruik	x					x		x	x	
	Substance use questionnaire	x						x			
	RAF GGZ Youth*				x		x		x		
	FAST Goal lists*				x		x		x		
	BPQ	x					x	x	x	x	
	FAST Goal lists*				x		x		x		
Mechanism of change	PSQ		x				x		x	x	
	NRI	x	x				x	x	x	x	
	IPPA	x					x	x	x	x	
	NPSI		x				x	x	x	x	
	NPQ	x	x				x	x	x	x	
	Parenting Practices	x	x				x	x	x	x	
	PDI	x	x				x	x	x	x	
	PCS-YR	x					x	x	x	x	
	BITI	x			x		x	x	x		
Moderator	Demographic questionnaire	x	x	x			x				
	ICU	x	x				x				
	APSD	x	x				x				
	Primary diagnosis (case file)				x		x				
	RAF GGZ Youth*				x		x				
	FAST evaluation form*				x				x		
	Treatment time registration				x				x		
	Direct treatment time		x					x			
	Relationship with Interventionist	x	x					x	x		
	TMS-F	x	x				x		x		
	PETS		x				x				
	Cooperation Scale	x	x	x					x		

*Note.* *Questionnaire is filled out as part of the standard FAST procedure. YSR = Youth Self Report; CBCL = Child Behavior Checklist; SDB = Self-report delinquent behavior; RAF GGZ Youth = Risk Assessment Instrument for Outpatient Forensic Mental Health Care Youth; FAST = Forensic Outpatient Systemic Therapy; BPQ = Basic Peer Questionnaire; PSQ = Parental Support Questionnaire; NRI = Network of Relationship Inventory; IPPA = Inventory of Parent and Peer Attachment; NPSI = Nijmeegse Parenting Stress Index; NPQ = Nijmeegse Parenting Questionnaire; PDI = Parenting Dimensions Inventory; PCS-YR = Psychological Control Scale Youth Report; BITI = Brief Irrational Thoughts Inventory; ICU = Inventory of Callous-Unemotional Traits; APSD = Antisocial Processes Screening Device; TMS-F = Treatment Motivation Scales for Forensic Outpatient Treatment; PETS = Parent Expectancies of Therapy Scale; Ju = Juvenile; Ca = Caregiver; Th = Therapist; CF = Case file analysis; JR = Judicial records; T1 = pre-test; M = monthly assessment; T2 = post-test; T3 = 6-month follow-up; T4 = 2-year follow-up

### Participants

In total, 200 FAST participants will be included in the study. The target group is diverse in terms of (comorbid) problems, but approximately 93% of the juveniles referred to FAST has a behavioral disorder [6] and they often grow up in families with multiple and complex problems. In FAST, 75% of juveniles is male.

#### Inclusion and exclusion criteria

Every juvenile and caregiver who receive FAST is considered for the study. FAST therapists determine whether clients meet inclusion and exclusion criteria during the standard FAST intake procedure. The inclusion criteria of FAST are: (1) Juvenile has an estimated IQ-score of 80 or higher and/or sufficient adaptive skills to benefit from the intervention; (2) Juvenile is aged 12–21 years old at intervention start; (3) Juvenile exhibits externalizing behavior that results in problems in at least two areas of life (family, school, leisure time), determined by clinical impressions based on referrer information and/or information from intake; (4) Juvenile has a medium to high recidivism risk, measured by the Risk Assessment Instrument for Outpatient Forensic Mental Health Care Youth (RAF GGZ Youth) [39]; (5) Presence of juvenile-caregiver relationship problems, as measured by the RAF GGZ Youth; (6) Juvenile has a diagnosis of a DSM-5 behavioral disorder, which is determined using case file analysis or a new diagnostic process; (7) Caregiver(s) and juvenile cannot be motivated to follow treatment at the treatment site after multiple attempts by the therapist; (8) Juvenile resides with their caregiver(s) or is expected to return to residing with caregiver(s) within the first two months of intervention.

The exclusion criteria of FAST are: (1) Juvenile exhibits severe psychiatric symptoms requiring admission; (2) Problem behavior of the juvenile is primarily caused by substance abuse problems and it is expected that treatment of the substance abuse problems will decrease the problem behavior; and (3) The safety of the therapist or family members cannot be guaranteed sufficiently. Additionally, clients that are not eligible to receive blended intervention are excluded from the study. These study exclusion criteria are: (1) Clients do not have an electronic device or suitable internet connection to receive blended care; (2) Clients have insufficient digital literacy to receive blended care; and (3) Families need a translator to receive the intervention.

#### Sample size calculation

Based on a MANOVA a priori power analysis, a group of *n* = 120 (*n* = 60 per group) will allow us to identify – with a power of 0.80, an alpha of 0.05 – small differences (d = 0.15) in effectiveness between FASTb and FASTr (G*power 3.1) [40]. To account for possible drop-out, which was approximately 20% in our previous comparable study [41], *n* = 200 participants will be recruited. Based on the number of juveniles referred to FAST at the treatment sites participating in this project (approximately 120 juveniles yearly), and participation rates of 70–90% in our earlier comparable studies [41, 42], it is considered feasible to include in total *n* = 200 juveniles and their caregivers within three years.

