### Procedure

During the intake, therapists evaluate whether the clients meet the inclusion and exclusion criteria for the study. In case of doubt, therapists consult the research team in order to determine whether exclusion criteria are met. Once determined that a family can start FAST treatment, therapists ask caregivers and juveniles permission to share their contact details with the researcher. If they agree, FAST clients are approached by the main researcher or research assistants, whom all have signed a non-disclosure agreement and provided a certificate of conduct. Eligible clients receive verbal and written information about the study. The researcher obtains written informed consent from juveniles and caregivers for own participation, and from caregivers/legal representatives for juveniles younger than 16 years. After obtaining informed consent, participating families are randomized to receive FASTb or FASTr. Randomization is done on the level of the treatment site using a computerized randomization in a 1:1 ratio. Randomization outcome is shared by the researcher with both participants and participants’ therapist.

During the study, participants (juveniles and caregivers) fill out main questionnaires three times: Prior to or during the first weeks of intervention (pre-test; T1), immediately after the intervention (post-test; T2), and 6 months after termination of the intervention (6 months follow-up; T3). Therapists fill out questionnaires at T1 and T2. In addition, during the intervention, juveniles and caregivers fill out short monthly questionnaires. The number of monthly questionnaires depends on the length of intervention, which differs between five and nine months. Further, case file analysis is used to retrieve questionnaires that are filled out by juveniles, caregivers, and therapists as part of the standard FAST procedure. Official recidivism data will be collected at two-year follow-up (T4) to determine longer-term effects. For an overview of the study, see Fig. 2.

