#### Effectiveness

Research questions related to the effectiveness of FASTb versus FASTr on the primary and secondary outcomes will be answered using co-variance analyses with a correction for multiple testing, with the pre-test (T1) score on the dependent variable as a covariate, the post-test (T2) and 6-month follow-up (T3) scores as the dependent variable, and the condition (FASTb or FASTr) as a factor. Dichotomous outcome variables will be tested with Chi-square analysis to compare the percentage of the FASTb and FASTr conditions. Recidivism data after two years (T4) will be analyzed using Kaplan Meyer and Cox survival analyses. Effect sizes will be computed as Cohen’s d, based on adjusted means and standard errors.

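### With 60 per group, the planned T1-adjusted ANCOVA has roughly 13% to 27% power for d = 0.15, not the stated 80%

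*Protocol article*

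**What the plan says.** Under Sample size calculation, the protocol article describes its method as "Based on a MANOVA a priori power analysis" run in G*Power 3.1. The target of that calculation is "small differences (d = 0.15) in effectiveness between FASTb and FASTr". The sample said to suffice is 120 in total, or 60 in each arm, and the error rates behind it are given as "with a power of 0.80, an alpha of 0.05". Recruitment is then set at 200, for which the stated reason is this: "To account for possible drop-out, which was approximately 20% in our previous comparable study". The section does not give the number of responses or measurements, the correlation between them, or whether the test is one- or two-sided.

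Under Plan of data analysis, Effectiveness, the primary and secondary outcomes are to be compared by "co-variance analyses with a correction for multiple testing, with the pre-test (T1) score on the dependent variable as a covariate". T2 and T3 scores are the dependent variables and condition is the factor. Procedure specifies "computerized randomization in a 1:1 ratio".

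**The concern.** A standardised difference of 0.15 is very small, and detecting it normally takes several hundred participants per arm. The stated combination of d, n, alpha and power therefore looks impossible for a two-group comparison of scores, even with baseline adjustment. The power statement also refers to a MANOVA, while the analysis section plans ANCOVAs with a multiplicity correction.

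The direction of the hypothesis raises the stakes. Aims of the study and Discussion expect the two versions to work equally well, and Conclusion links the usefulness of blended care to its being no worse than face-to-face treatment. A non-significant comparison is thus the hoped-for result. A reader told that d = 0.15 was detectable with 80% power would take such a result to exclude even small differences.

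**Working it through.** **Inputs from the protocol article.** Alpha 0.05, power 0.80, d = 0.15, 60 per group, 1:1 allocation, 200 recruited, drop-out about 20%.

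**Assumptions.** Two-sided test, SD = 1, individual randomisation with no clustering. The correlation r between T1 and outcome is not given, so a range is shown.

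**1. The stated figure, taken as written.** For ANCOVA, approximately:

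n per arm = 2(1 − r²)(1.96 + 0.8416)² / d²

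With d = 0.15 this gives 698 (r = 0), about 523 (r = 0.5), 447 (r = 0.6), 356 (r = 0.7) and about 251 (r = 0.8). The stated 60 is not reproduced. Testing one-sided lowers the unadjusted figure only to 550.

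**2. Power at d = 0.15.** The noncentrality parameter is d / √(1 − r²) × √(n/2), referred to a noncentral t distribution. With n = 60, the r = 0 value is 0.15 × √30 = 0.82. Dividing by √(1 − r²) gives 0.82/0.80 = 1.03 at r = 0.6, 0.82/0.714 = 1.15 at r = 0.7 and 0.82/0.60 = 1.37 at r = 0.8. About 2.80 is needed for 80% power.

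| Analysed per arm | r = 0 | r = 0.6 | r = 0.7 | r = 0.8 |
|---|---|---|---|---|
| 60 | 13% | 17% | 21% | 27% |
| 80 (200 less 20%) | 16% | 22% | 26% | 35% |
| 100 (no loss) | 18% | 26% | 32% | 42% |

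**3. Correlation needed for the claim.** Setting 0.82 / √(1 − r²) = 2.80 gives √(1 − r²) = 0.293, so r is about 0.956.

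**4. Detectable difference with 80 per arm** (80% power, two-sided 0.05, t-based): d = 0.45 (r = 0), 0.36 (r = 0.6), 0.32 (r = 0.7). Divided by 0.15, these are 3.0, 2.4 and 2.1 times the claimed value. The planned multiplicity correction raises them further. The protocol names neither a method nor a number of tests. Purely as an illustration, Bonferroni over 10 tests would give about 0.47 (r = 0.6) to 0.58 (r = 0).

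**5. Settings that do return about 120.**
- d = 0.15 (f = 0.075) in a group-by-time interaction with 3 measurements correlated 0.8: N = 116 to 118.
- 0.15 read as f (d = 0.30), between-groups test on 3 uncorrelated measurements: N = 120.
- 0.15 read as f-squared (d about 0.77), MANOVA with 10 responses: N = 118.

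None of these settings is stated, and none is the analysis in the Effectiveness section.

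**6. Drop-out step.** 120 / (1 − 0.20) = 150, and 200 × 0.80 = 160. Going from 200 to 120 corresponds to 1 − 120/200 = 40% loss.

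**The case against.** The strongest defence is that the calculation was for a MANOVA, and that a repeated-measures form of it could be legitimate. A reader might infer from the three-measurement case that 120 works only with a correlation near 0.8. That is too strong. Table 1 lists the YSR, CBCL and SDB at T1, T2, T3 and monthly, and treatment lasts five to nine months, which makes about 8 to 12 occasions. A group-by-time test at f = 0.075 and N = 120 then has power of about 0.77 with 8 occasions at correlation 0.6, 0.89 at 0.7, and 0.78 with 12 occasions at 0.5. So some repeated-measures design could come close to the stated power. This does not rescue the claim, because the Effectiveness section uses T2 and T3 scores adjusted for T1. The monthly forms are also shortened item sets on a different response scale, introduced under Design to study mechanisms of change.

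A reader might also infer that the authors mislabelled f or f-squared as d. The two readings imply different effects (0.30 and about 0.77), and the document confirms neither.

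The drop-out arithmetic might be read as a shortfall, or as a hidden assumption of 40% loss. It is neither: the protocol makes no such assumption, and 160 expected completers exceed the 120 required. The figure is unexplained but conservative.

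Finally, the details of the multiplicity correction are commonly left to an analysis plan, so their absence is no defect. The correction matters here only because it moves the true power further below the stated value. Any count of tests is the reader's own, and d does not describe the dichotomous and survival outcomes.

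**Conclusion.** The power statement is wrong as written for the planned analysis. At d = 0.15 the ANCOVA has about 13% to 27% power with 60 per arm (r = 0 to 0.8). For r = 0 to 0.7 it has about 16% to 26% with 80 per arm and 18% to 32% with 100 per arm. Over those same correlations, with 60 to 100 per arm, a true difference of 0.15 would be missed in about 68% to 87% of trials. Recruiting 200 does not repair this.

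The size depends on the assumed r and on the two-sided, unclustered setting. The conclusion does not, because 80% power with 60 per arm needs a correlation of about 0.956. The documents do not show how 0.15 and 120 came to be paired, and they do not support saying that no MANOVA could yield 120. The drop-out step is a minor side remark.

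**What to change.** In Sample size calculation, remove the claim about small differences at d = 0.15 and restate the sensitivity for the analysis that will be run, for example:

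> With 200 randomised and 20% drop-out, about 160 (80 per arm) are analysed. ANCOVA then has 80% power at two-sided 0.05 for d of about 0.45 (assumed T1 correlation 0), 0.36 (0.6) or 0.32 (0.7), before correction for multiple testing, which raises the detectable difference further.

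The assumed correlations should be labelled as assumptions, or replaced by a value with a source. If the authors want to keep the G*Power result, they should state the test, the effect metric, the number of measurements and the correlation, and say that it does not describe the ANCOVA. The drop-out sentence should say that 200 leaves about 160 completers, more than the 120 named.

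The cost is one corrected paragraph and a less favourable stated sensitivity. Enrolment, data collection and the analysis itself do not change.

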### Procedure

During the intake, therapists evaluate whether the clients meet the inclusion and exclusion criteria for the study. In case of doubt, therapists consult the research team in order to determine whether exclusion criteria are met. Once determined that a family can start FAST treatment, therapists ask caregivers and juveniles permission to share their contact details with the researcher. If they agree, FAST clients are approached by the main researcher or research assistants, whom all have signed a non-disclosure agreement and provided a certificate of conduct. Eligible clients receive verbal and written information about the study. The researcher obtains written informed consent from juveniles and caregivers for own participation, and from caregivers/legal representatives for juveniles younger than 16 years. After obtaining informed consent, participating families are randomized to receive FASTb or FASTr. Randomization is done on the level of the treatment site using a computerized randomization in a 1:1 ratio. Randomization outcome is shared by the researcher with both participants and participants’ therapist.

During the study, participants (juveniles and caregivers) fill out main questionnaires three times: Prior to or during the first weeks of intervention (pre-test; T1), immediately after the intervention (post-test; T2), and 6 months after termination of the intervention (6 months follow-up; T3). Therapists fill out questionnaires at T1 and T2. In addition, during the intervention, juveniles and caregivers fill out short monthly questionnaires. The number of monthly questionnaires depends on the length of intervention, which differs between five and nine months. Further, case file analysis is used to retrieve questionnaires that are filled out by juveniles, caregivers, and therapists as part of the standard FAST procedure. Official recidivism data will be collected at two-year follow-up (T4) to determine longer-term effects. For an overview of the study, see Fig. 2.

Given the complexity of the problems the target group faces, which often adversely affects the motivation to participate in treatment or research, researchers adjust the data collection to the preferences and agenda of the participants for timing and location (by (video) phone calls or at the homes of the families). Trained research assistants are available to assist with filling out the questionnaires, e.g., by taking them in interview form, and to carry out monthly assessments (online or by phone). Participants receive a financial compensation for filling out the questionnaires: 15 euros for T1, T2, and T3, and 1 euro per monthly assessment.

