**Methods:**

A randomized controlled trial (RCT) will be carried out. Participants (*N* = 200) will be randomly assigned to FASTb (*n* = 100) or FASTr (*n* = 100). Data collection will consist of self-report questionnaires and case file analysis, and include a pre-test at the start of the intervention, a post-test immediately after the intervention, and a six month follow-up. Mechanisms of change will be investigated using monthly questionnaires of key variables during treatment. Official recidivism data will be collected at two-year follow-up.

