#### Primary outcomes

##### Externalizing behavior

Externalizing behavior will be measured at T1, T2, and T3 using juvenile self-report on the Externalizing scale of the Youth Self Report (YSR) [43] and caregiver report on the Child Behavior Checklist (CBCL) [44]. Both the YSR and CBCL contain 33 items, which are rated on a 3-point Likert scale ranging from 0 = *never* to 2 = *often*.

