Therapist-client alliance will be measured at T2 using juvenile and caregiver report on the Relationship with Interventionist [60]. The Relationship with Interventionist contains 12 items, which are rated on a 6-point Likert scale ranging from 1 = *totally disagree* to 6 = *totally agree*.

Treatment motivation of juveniles and caregivers will be measured at T1 and T2 using self-report on the Treatment Motivation Scales for Forensic Outpatient Treatment (TMS-F) [61]. The TMS-F contains 16 items, which are rated on a 5-point Likert scale ranging from 1 = *totally disagree* to 5 = *totally agree*.

Treatment expectancies will be measured at T1 using caregiver report on the Parent Expectancies of Therapy Scale (PETS) [62, 63], and therapist report at T1 and T2 on one item asking how effective they think the assigned version of FAST (FASTb or FASTr) is in comparison to the other version of FAST. Therapists rate the question on a 5-point Likert scale ranging from 1 = *much less effective* to 5 = *much more effective*. The PETS contains seven items, which are rated on a 5-point Likert scale ranging from 1 = *low expectations* to 5 = *high expectations*.

Treatment cooperation will be measured at T2 using juvenile, caregiver, and therapist report on the Cooperation Scale [60]. The Cooperation Scale contains five items, which are rated on a 6-point Likert scale ranging from 1 = *totally disagree* to 6 = *totally agree*.

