### Plan of data analysis

Data will be analyzed according to the intention-to-treat principle and will also be analyzed separately for the completers only. Little’s test will be used to test whether data is missing at random. If so, missing data will be imputed so that all participants can be included in the analyses. Possible baseline differences in demographic characteristics between the participating and non-participating FAST-clients will be checked by means of chi-square analyses and independent t-tests to investigate the representativity of the included sample. In addition, possible baseline differences in demographic characteristics and outcome variables between the FASTb and FASTr condition will be checked by means of (M)ANOVA (continuous variables) and chi-square analyses (categorical variables). If (some of) these variables show significant differences between FASTb and FASTr conditions, they will be entered as covariates in all (regression) models testing the effectiveness of the intervention.

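### The pre-test used as ANCOVA covariate may be completed after the arm is known and treatment has begun, which can bias the adjusted effect on questionnaire outcomes

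*Protocol article*

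**What the plan says.** All references are to the protocol article.

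- **Procedure, allocation.** "After obtaining informed consent, participating families are randomized to receive FASTb or FASTr". Then: "Randomization outcome is shared by the researcher with both participants and" the family's therapist.
- **Procedure, timing of T1.** The first main questionnaires are completed "Prior to or during the first weeks of intervention (pre-test; T1"). No maximum number of weeks is set, and the same section lets the timing of data collection follow the family's preference. The Abstract is a little tighter: "include a pre-test at the start of the intervention".
- **Treatment characteristics.** At T1 therapists answer an item "asking how effective they think the assigned version of FAST (FASTb or FASTr) is in comparison to the other version of FAST", so for therapists the arm is known at T1.
- **Primary outcomes.** "Externalizing behavior will be measured at T1, T2, and T3 using juvenile self-report" and caregiver report. Both informants are told the arm.
- **Effectiveness.** The model is a covariance analysis "with the pre-test (T1) score on the dependent variable as a covariate".
- **Plan of data analysis.** Demographic and outcome variables are compared between arms at baseline. "If (some of) these variables show significant differences between FASTb and FASTr conditions, they will be entered as covariates" in all models that test effectiveness.

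**The concern.** ANCOVA gives an unbiased arm comparison when the covariate cannot be affected by allocation. A questionnaire completed by someone who knows the arm, possibly after some weeks in it, does not meet that condition. If part of a real difference between arms has already reached T1, the adjustment subtracts some of it. If knowing the arm changes how people answer at T1, the adjustment can create a difference or alter its sign.

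The covariate rule adds a second route. A T1 difference caused by allocation would count as a baseline imbalance and be adjusted for in every effectiveness model.

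T1 motivation (TMS-F) and caregiver expectancy (PETS, measured only at T1) are also planned moderators. If they are answered after disclosure, they are no longer characteristics that precede allocation.

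The trial expects the two versions to be equally effective. Where a real difference has partly reached T1, the bias shrinks the estimate toward that expected result.

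**Working it through.** The plan states no figure on this point, so there is none to reproduce. The documents give neither the slope nor any T1 shift; both are assumptions below. Outcomes are in SD units with equal SDs at T1 and T2, so slope equals correlation.

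**Formula.** Adjusted effect = tau - b × delta, where tau is the arm difference at T2, delta the arm difference already in T1, and b the within-arm slope of T2 on T1.

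**1. Part of a real effect is already in T1.** Let T1 carry 10% to 30% of tau, with b from 0.5 to 0.7.
- Smallest loss: 0.5 × 0.10 = 5% of the effect.
- Largest loss: 0.7 × 0.30 = 21%.
- For tau = 0.30 SD the estimate becomes 0.285 to 0.237 SD.

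**2. Reporting shift at T1 only.** With delta = 0.2 and tau = 0:
- 0.5 × 0.2 = 0.10 and 0.7 × 0.2 = 0.14.
- The spurious effect is 0.10 to 0.14 SD, opposite in sign to the shift. For scale, the sample size section names d = 0.15 as the difference to detect.

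**3. The same reporting shift persists to T2.** Both scores move by 0.2:
- 0.2 - b × 0.2 = 0.2 × (1 - b), which is 0.10 at b = 0.5 and 0.06 at b = 0.7.
- The unadjusted bias would be 0.20, so here the late T1 offsets part of it.

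**4. Error rates.** Simulation with 80 analysed per arm (200 less 20% dropout, split 1:1), b = 0.6, 4000 runs.

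| tau | T1 shift | mean estimate | rejection rate |
|---|---|---|---|
| 0 | 0 | 0.00 | 5.1% |
| 0 | 0.1 | -0.06 | 7.6% |
| 0 | 0.2 | -0.115 | 15.4% |
| 0.30 | 0 | 0.30 | 65% |
| 0.30 | 0.06 | 0.27 | 55% |
| 0.30 | -0.15 | 0.39 | 87% |

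The means agree with the formula, for example -0.6 × 0.2 = -0.12.

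**5. Baseline test.** With 100 per arm, a T1 shift of 0.1 SD is significant at 0.05 (two-sided) in 10.5% of trials, and one of 0.2 SD in 29.3%. An allocation effect on T1 can thus bring further covariates into the models.

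**6. Could the adjustment remove the whole effect?** That needs b × delta = tau. With tau = 0.15 and b = 0.6, delta = 0.15 / 0.6 = 0.25 SD, a larger arm difference at T1 than at T2.

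**The case against.** **The order is not stated outright.** A reader might infer that every pre-test follows randomisation and disclosure. The text does not say so. It dates T1 against the intervention, not against randomisation, and a T1 at the consent contact fits the wording. The flowchart (Fig. 2) could not be consulted. The therapist item shows that therapists know the arm at T1, but it does not date the YSR, CBCL or SDB. This stands: the claim is that T1 may fall after allocation for some families. A T1 completed during the first weeks of the intervention necessarily does.

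**Early contact is largely shared.** The bias needs a difference between arms at T1, not just treatment exposure. FASTb is described as nearly the same in content. Table 2 makes intake and the first appointment after it face-to-face in both arms, and lists eHealth and the app under the treatment stage, after a one-month pre-treatment stage. The 50% online share is an average over the whole intervention. This also stands, and it makes a large early treatment effect on T1 unlikely. It does not cover a reporting effect, which needs only knowledge of the arm.

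**A persistent reporting shift is partly cancelled.** Step 3 bears this out. The cancellation is uncontrolled, however, and the same mechanism cancels real effects. Reporting bias at T2 in an open trial is a separate matter that the timing of T1 cannot cure.

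**Some outcomes are not exposed.** Two-year recidivism uses survival analysis and dichotomous outcomes use chi-square tests, so the planned tests have no T1 covariate. The RAF GGZ Youth score is used for eligibility, so its T1 value may precede randomisation. The SDB asks about the past year, so a few weeks of treatment change little of its window.

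**Conclusion.** The point holds in a limited form. The plan allows the ANCOVA covariate to be measured after allocation, after disclosure and during assigned treatment, with no limit in weeks. It then conditions on that score and may add further T1 outcome variables chosen by significance test. The affected measures are the YSR, CBCL, BPQ and self-reported substance use, the SDB to a lesser degree, and the T1 motivation and expectancy moderators.

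The size is unknown and probably modest. The range of 0.06 to 0.14 SD rests on an assumed 0.2 SD reporting shift and assumed slopes of 0.5 to 0.7; its upper part (0.10 to 0.14) applies only if the shift has gone by T2. The 5% to 21% loss rests on an assumed T1 share that the documents do not support, and the shared early contact points to the low end.

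Two further readings should not be drawn. Step 6 shows that removal of the whole arm effect is implausible. That families who withdraw on learning their arm will lack a T1 depends on an order of events that the text does not fix.

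**What to change.** **For families still to be enrolled.** State in the Procedure that the juvenile and caregiver T1 questionnaires are completed after consent and before the allocation is disclosed, preferably before randomisation. The therapist item on the assigned version necessarily comes after disclosure and should be described as a post-allocation measure. This reorders existing steps and adds no assessment. The cost is that allocation is released later for some families, which matters in a group that is hard to schedule. Intake and the first appointment have the same format in both arms, so that format does not depend on knowing the arm.

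**For families already enrolled.** Record the T1 date relative to randomisation, disclosure and first session, and add two sensitivity analyses:

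1. One restricted to families whose T1 preceded disclosure. It uses a cleaner covariate but loses randomised families.
2. One that keeps all randomised families and does not condition on post-allocation T1 scores. It loses precision: dropping the covariate altogether multiplies the variance by 1 / (1 - r²), which is 1.33 at r = 0.5 and 1.96 at r = 0.7.

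**Covariate rule.** Do not add T1 outcome variables as covariates on the strength of a significance test when T1 was taken after allocation.

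**Moderators.** Report whether T1 motivation and expectancy were measured before or after disclosure, and interpret their interactions accordingly. Dating T1 and running the extra analyses costs almost nothing and remains possible after recruitment closes, provided the dates can be recovered.
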